#### Development of the AI-generated digital intervention based on the IMB model

The 1-month digital intervention will be generated, aiming to promote awareness and utilization of primary healthcare services, particularly those offered by DHCs. Twelve of the health-related messages will be sent through the instant messaging platform WhatsApp 3 times per week. This aims to reinforce older adults’ knowledge of DHCs gained during the in-person intervention and provide further motivation for utilizing the available services.

The digital intervention is structured into four sequential weekly themes, with each week targeting a key component of the District Health Center primary healthcare model. The first is primary prevention, which introduces the health promotion activities provided. The second is secondary prevention, and it explains the importance of regular health assessment. The third is tertiary prevention, this promotes chronic disease management and rehabilitation support. The final week provides an overall summary, and inserts information on DHC enrolment requirements (see Table 2).

**Table 2 tab2:** Framework of intergenerational digital intervention on primary healthcare service utilization.

Day	Component	Digital intervention content
Week 1—primary prevention		
Mon	Information	Introduction to healthy lifestyle promotion activities
Wed	Motivation	Reflection on suitable health promotion services and healthy routines
Fri	Behavioral skills	Guide for access to health promotion services
Week 2—secondary prevention		
Mon	Information	Explanation on health assessments of hypertension and diabetes screening
Wed	Motivation	Evaluation on personal health status
Fri	Behavioral skills	Guide for access to health assessments
Week 3—tertiary prevention		
Mon	Information	Information on chronic disease management and rehabilitation services
Wed	Motivation	Reflection on priorities related to disease risk
Fri	Behavioral skills	Guide for access to chronic disease management and rehabilitation interventions
Week 4—summary		
Mon	Information	Overview of DHC appointment process
Wed	Motivation	Prompt encouraging enrolment and scheduling of DHC appointments
Fri	Behavioral skills	Final reminder with enrolment details and contact information for DHC services

Each week will include three messages aligned with the IMB Model, delivered on Monday, Wednesday, and Friday, with each message targeting a key component of the IMB Model. The Information component will use videos to deliver core health information through accessible and engaging media. The Motivation component will be delivered through infographics and will inspire and motivate behavior change through behavior change theory-based content. The Behavioral Skills component will consist of text messages providing practical support to facilitate action, such as access guidelines, center addresses, and telephone numbers.

To ensure ease of use, videos and infographics would be delivered as files that can be viewed directly within the WhatsApp interface without requiring external links. During home visits, participants will receive guided WhatsApp setup and comprehensive hands-on demonstrations for the viewing of all message types. Ongoing support is provided throughout the intervention period through WhatsApp group and accessible helplines.

Generative Pre-trained Transformer 4 (GPT-4) will be employed as the primary platform for the generation of a large 60-message intervention bank. The format would include text messages, infographic content, and video frameworks. The AI model will be guided through role-specific prompting as a healthcare researcher, with detailed task descriptions, content specifications, target audience information, and output rules. Official District Health Centers documentations would be provided for the AI model as reference.

The content of text messages and the framework of infographics and videos will be generated by GPT-4, followed by design and fine-tuning for maximum effectiveness (29). Project research assistants will check and adjust the materials for factual accuracy, contextual relevance, and overall readability. Given that the target audience consists of older adults with limited comprehension levels, the content will be kept simple through the limitation of words and minimization of technical terminologies. All refined AI-generated materials will undergo review by qualified public health professionals to ensure compliance with established health communication standards.

Subsequently, a user-centered design process will be conducted (see Figure 2). There will be three iterative rounds of message evaluation, involving 10 participants per round. Each round will include both quantitative and qualitative assessments to guide message refinement. For the quantitative assessment, participants will independently rate each message using a 5-point Likert scale (1 = strongly disagree to 5 = strongly agree) across six dimensions based on McGuire’s Model of Communication and Persuasion: exposure, attention, comprehension, acceptance, retention, and action (36) (see Table 3). For the qualitative assessment, participants will engage in WhatsApp-based feedback, where they will be prompted to provide brief comments on each message. They will be asked to identify specific elements they liked, as well as to elaborate on any negative experiences if applicable.

**Figure 2 fig2:**
[figure not shown]
The AI-generated and user-centered digital intervention design process. The initial digital intervention message bank undergoes three iterative rounds of refinement, incorporating both quantitative and qualitative user feedback from older adults, to develop the final, optimized message bank.

**Table 3 tab3:** Older adults quantitative and qualitative evaluation on AI-generated messages.

Item	Contents					
Exposure	The material is shown clearly on my mobile device.	1 = Strongly disagree	2 = Disagree	3 = Neutral	4 = Agree	5 = Strongly agree
Attention	The material looks good and catches my attention.	1	2	3	4	5
Comprehension	The material is easy to understand.	1	2	3	4	5
Acceptance	The material is clear and non-judgmental.	1	2	3	4	5
Retention	The material is memorable and stays with me.	1	2	3	4	5
Action	The material motivates me to use DHC services.	1	2	3	4	5

Iterative refinement will be conducted using a review–refine–retest cycle. After each round, messages will be revised based on both quantitative ratings and qualitative input and then retested in the subsequent round. First, all messages with low mean scores on any evaluation dimension will be identified for major revision. Then, to guide refinement, qualitative feedback will be analyzed to identify recurring issues and themes. These comments will be categorized into message-specific and general remarks. The message-specific comments will guide targeted major revisions to individual messages, while the broad comments will be applied as minor revisions across all messages of the same format.

### Control group: general intervention

The control group will receive standard care, which is adapted from the intervention package as outlined in our recent publications, referred to as the *Standard Generations Connect Package* (15, 16). The Standard GC Package is delivered through two major approaches: a home-based intervention and a digital intervention. The home-based intervention is a 90-min face-to-face session, during which trained student interns collect health assessment data and deliver theme-based, tailored health interventions. The interventions are focused on four key areas: non-communicable disease (NCD) prevention, psychosocial health, digital health literacy, and infectious disease prevention.

Non-communicable disease prevention: Reduce the risk of non-communicable diseases by encouraging a healthy lifestyle. Older adults will receive guidance on physical activity, healthy dietary choices, smoking cessation, and alcohol moderation.Mental health and wellbeing: Enhance the mental wellbeing of older adults by promoting positive thinking, emotional resilience, and social engagement. Participants will be encouraged to adopt relaxation techniques to manage stress. They will also be introduced to practical strategies and resources that support psychosocial health and wellbeing.Digital Health literacy: Strengthen older adults’ ability to find, evaluate, and use electronic health information by guiding them to use WhatsApp for contacting health professionals and connecting with family or friends, using QR code scanners to acquire health information from printed materials, and downloading and using mobile health service applications, such as HA Go and Electronic Health Record Sharing System (eHealth).Infectious disease prevention: Enhance knowledge and practices related to seasonal influenza by educating on hygiene, handwashing techniques, government vaccination benefits, and mask-wearing.

Participants will receive the *standard Generations Connect Blue Folder*, which contains relevant health education leaflets. Student interventionists will explain the leaflet content in a simplified and personalized manner, suited to the comprehension levels of older adults. To prepare them for the upcoming digital intervention, a dedicated WhatsApp group will be created for each participant. Students will guide participants on how to access and use WhatsApp and ensure they are able to navigate the app confidently. Over the following month, participants in the control group will receive daily digital messages via WhatsApp, providing general health advice based on the four themes of the *Standard Generations Connect Package*.

### Intervention group: primary healthcare service utilization package

The intervention group will receive the *Primary Healthcare Service Utilization Intervention Package,* in addition to the *Standard Generations Connect Package*. The main focus for the intervention group is primary healthcare service engagement; it will promote the use of primary healthcare services, particularly those offered by District Health Centers, to support health promotion, regular health assessments, chronic disease management, and community rehabilitation. Older adults will receive guidance on the benefits of utilizing these services and will be encouraged to undergo routine health check-ups. Participants will strengthen their understanding of DHCs, increase their awareness of available services, and be motivated to actively utilize them.

The intervention is similarly delivered through two major approaches: home-based intervention and a digital intervention. The home-based intervention is a 90-min face-to-face session, during which trained student interns collect health assessment data and deliver theme-based, tailored health interventions. The digital intervention is a 1-month follow-up support involving daily messages via instant messaging apps (e.g., WhatsApp) that include health-related infographics, videos, and personalized advice.

#### Home-based intervention

The face-to-face proactive home-based intergenerational intervention lasts up to 90 min. Trained student interventionists will conduct baseline health assessments and deliver interventions in pairs. Written consent will be obtained from participants before the assessment begins. The assessment process is flexible, adapting to older adults’ responses. They will conduct the baseline assessment in a semi-structured manner, engaging participants in natural conversations while covering questionnaire items. The questions are read aloud to older adults, and responses are provided verbally.

Participants in the intervention group will receive a *PHC Green Folder*, in addition to the standard *GC Blue Folder*. The *PHC Green Folder* contains targeted materials related to primary healthcare services, including health education leaflets with QR codes linking to online resources, aimed at promoting awareness and encouraging the use of DHC services. Student interventionists will explain the leaflet content and tailor discussions to address the specific health needs of each older adult. The home-based intervention materials are aligned with the Information-Motivation-Behavioral Skills Model (see Table 4). At the end of the intervention, student interventionists will set up individual one-on-one WhatsApp chat groups with the older adults to facilitate the subsequent one-month digital intervention.

**Table 4 tab4:** Framework of home-based intervention on primary health care service utilization.

Component	Intervention details
Information	*DHC Information Pamphlet*—Covers DHC services, the importance of primary healthcare, and the benefits of regular health assessments and health promotion.
Motivation	*Experience Sharing Pamphlet*—Presents experiences of older adults who have positively benefited from using DHC services, based on qualitative findings from the *Generations Connect* project.
Behavioral skills	*Visit Guide Pamphlet*—Provides maps, transportation options, and opening hours to help participants locate their district-specific DHC, along with guidance on securing a booking.
Behavior	*Health Decision-making Pamphlet*—Encourages older adults to make informed health decisions and take actions to improve their wellbeing, strengthening self-efficacy.

## Outcomes

### Feasibility outcomes

Feasibility and acceptability indicators will be measured at three-month follow-up (37). Feasibility outcomes will be assessed using recruitment rate, retention rate, dose received through percentage of message views and participant engagement through interaction with digital messages. Other indicators include dose delivered, in which intervention fidelity is measured using a protocol checklist and visit time record. Acceptability outcomes include participant satisfaction with the home-based intervention and the 4-week follow-up digital intervention.

### Primary outcomes

The primary outcome is the proportion of older adults who become DHC members at 3 months. It is a single-item self-report measure of whether participant has joined the District Health Center (Yes/No).

### Secondary outcomes

Secondary outcomes assessed are the proportion of older adults utilizing DHC services, experience and satisfaction with DHC services, health status, lifestyle risk factors, eHealth literacy, and infectious disease prevention behaviors after 3 months. A single-item measure will determine the DHC service utilized by older adults. The item will examine which services are accessed across four core DHC areas of health promotion, health assessments, chronic disease management, and community rehabilitation. Emphasis is placed on the utilization of health promotion activities and regular health assessments, as the utilization of these services is independent of participants’ health status. Health status consists of physical health, quality of life, overall psychological health, loneliness, depression, and anxiety. Modifiable lifestyle risk factors for non-communicable chronic diseases include physical activity, diet, alcohol consumption, and smoking habits.

### Data collection

The study will use a mixed-methods design to construct a comprehensive understanding of the educational health communication intervention on DHC enrollment.

#### Quantitative measurements

Participants’ data will be collected using a self-administered survey at baseline and a telephone survey at 1, 3, and 6 months after the intervention. The baseline questionnaire includes demographics (9 items) and a self-constructed scale on DHC membership and utilization (17 items). Other scales on habits and wellbeing are also included in the questionnaire, such as healthcare service utilization (2 items), physical health (7 items), exercise habits [7 items, using validated IPAQ-SF (38)], dietary practices (5 items), smoking [3 items, using validated HSI (39)], alcohol consumption [3 items, using validated AUDIT-C (40)], psychosocial health and lifestyle [28 items, using validated WHO-5 (41), UCLA 3-item loneliness scale (42), PHQ-9 (43), and GAD-7 (44)], e-health literacy and mobile phone/app usage [29 items, using validated DHLI (45)], and infectious disease prevention behavior [15 items, using IPBS-I (46)].

The 1-month, 3-month, and 6-month follow-up surveys included similar items (demographics excluded), the 3-month follow-up would assess feasibility and acceptability. The 1-month, 3-month, and 6-month follow-up survey will be conducted via telephone.

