### Randomization, allocation, and blinding

The recruiting NGO health centers in three geographical areas will be randomized, using a computer-generated sequence, to either the intervention or control arm in a 1:1 ratio. Due to the nature of the study design and intervention, blinding of participants and intervention providers is not feasible. However, the outcome assessors, statistical analysts, and other investigators involved remain blinded to group allocation.

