## Discussion

### Limitations

Key limitations are in the DHC membership verification, smartphone-dependent intervention delivery, and generalizability of findings. The primary outcome of DHC membership is assessed through participant self-report since direct access to official enrolment records is not available to the research team for objective verification. The questionnaire will include questions regarding participation in activities within the DHC to help assess enrolment status, as membership is required for participation.

Intervention delivery depends on smartphone ownership and WhatsApp use. The intervention is only available to individuals who have access to a smartphone and are able to use WhatsApp. Individuals with very limited digital literacy may experience barriers to viewing and engaging with the digital intervention. This exclusion of non-smartphone users can also disproportionately affect highly socioeconomically disadvantaged individuals who lack mobile phone ownership or internet access, and those who do not use smartphones by choice. This raises ethical considerations regarding the exclusion of populations who are already socially and digitally marginalized. Such exclusion may compromise equitable access to the intervention and should be carefully considered for the planning of future implementation.

The generalizability among older adults is limited due to the unique target participant sample of underprivileged older adults recruited through NGOs, which serve as one of their main community healthcare sources. This limits the representativeness of the sample for the broader well-off older adult population using other healthcare resources. In addition, Hong Kong has unique healthcare system and digital features that limit generalizability. The tertiary sector of healthcare is well developed, alongside an emerging policy focus on primary health care system and District Health Center network. In terms of smartphone penetration, it is notably high (90.7%) among local older adults. As a result, transferability of study results beyond Hong Kong should be cautiously considered, accounting for differences in healthcare development and digital access conditions.

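### The 3-month primary outcome is an uncorroborated self-report from unblinded participants, only one arm of whom is urged to enrol, and assessor blinding cannot protect it from over-reporting that differs by arm

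*Protocol article*

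**What the plan says.** All references are to the Protocol article.

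- **Outcome and time point** (Primary outcomes): "The primary outcome is the proportion of older adults who become DHC members at 3 months". On the measure: "It is a single-item self-report measure of whether participant has joined the District Health Center (Yes/No").
- **Mode** (Quantitative measurements): "The 1-month, 3-month, and 6-month follow-up survey will be conducted via telephone". The follow-up surveys repeat items similar to those at baseline, and "the 3-month follow-up would assess feasibility and acceptability".
- **What acceptability means** (Feasibility outcomes): "Acceptability outcomes include participant satisfaction with the home-based intervention and the 4-week follow-up digital intervention".
- **Blinding** (Randomization, allocation, and blinding): participants and providers cannot be blinded, but "the outcome assessors, statistical analysts, and other investigators involved remain blinded to group allocation".
- **Who is urged to enrol**: Table 2 gives the intervention arm a week-4 prompt to enrol and a final reminder with enrolment details, and Table 4 adds DHC pamphlets at the home visit. The four control themes (Control group: general intervention) do not include DHC enrolment.
- **Verification** (Limitations): official enrolment records are not available to the team. The stated partial check is this: "The questionnaire will include questions regarding participation in activities within the DHC to help assess enrolment status, as membership is required for participation".
- **Baseline** (Home-based intervention): the student interventionists who deliver the intervention also carry out the baseline assessment.

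**The concern.** Blinding the assessor protects an outcome when the assessor's judgement enters the measurement. Here it hardly does. The participant supplies the answer, knows what was received and, in one arm only, has been encouraged over a visit and a month of messages to do the thing being asked about. A wish to please, or confusion between having been told about a DHC and having joined one, would push answers towards yes mainly in the intervention arm. The bias would then favour the intervention.

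The named cross-check does not close the gap. Activity in a DHC supports a claim of membership, but it is also self-reported, and it says nothing about a person who enrolled and has not yet attended. Such people are true successes on the primary outcome, so the check cannot separate them from a false yes.

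The trial is a pilot, but its results are meant to inform the sample size of a full-scale trial (Sample size planning). An inflated difference would carry into that planning.

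**Working it through.** **1. The plan's own figure.** Three regions × 2 NGO partners = 6 clusters, and 6 × 30 = 180, as stated. With 1:1 allocation that is 90 per arm. No stated figure is wrong on this point.

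**2. Does assessor blinding reach the bias?** Suppose the caller is perfectly blinded. The participant still knows the package received, and the yes/no is still the participant's alone. The calculation below contains no term for what the caller knows, so its result is the same with or without a blinded caller.

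**3. Size, by assumption.** Let *p* be true uptake, equal in both arms (no true effect), and *f* the share of intervention non-members who wrongly say yes, with none in control.

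Observed intervention proportion = *p* + *f*(1 − *p*); observed control proportion = *p*; spurious difference = *f*(1 − *p*).

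Neither *p* nor *f* is given in the article. The top value of *p*, 28.9%, is borrowed from the membership rate of the earlier community study in the Introduction. It is a reference value only, since this trial enrols non-members.

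| True uptake *p* | *f* = 5% | *f* = 10% | *f* = 15% |
|---|---|---|---|
| 10% | 0.90 × 0.05 = 4.5 points | 9.0 | 13.5 |
| 20% | 0.80 × 0.05 = 4.0 points | 8.0 | 12.0 |
| 28.9% | 0.711 × 0.05 = 3.6 points | 7.1 | 10.7 |

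In people, at *p* = 20% and *f* = 10%: 18 of 90 are true members and 72 are not. False yes answers number 7.2, giving 25.2/90 = 28.0% against 20.0%. About seven people produce the 8 points.

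**4. If control participants over-report too.** With a control rate *f*₀ the difference is (*f* − *f*₀)(1 − *p*). At *p* = 20%, *f* = 10% and *f*₀ = 5% it is 0.05 × 0.80 = 4.0 points. Equal rates give no spurious difference when there is no true effect. Only the excess in the intervention arm matters.

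**5. What corroboration would do.** Suppose a share *c* of true members can be corroborated, equal in both arms, and a share *g* of false yes answers slips through. With no true effect the corroborated difference is *c p* + *g f*(1 − *p*) − *c p* = *g f*(1 − *p*). At *p* = 20% and *f* = 10% this is 8 points × *g*: nil if no false yes passes, 4 points if half do. True members left uncorroborated lower both proportions but do not by themselves create a difference.

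**The case against.** A reader might infer something stronger: that asking about satisfaction in the same 3-month call reveals the arm, so the claimed assessor blinding fails at the primary time point. The article does not support that. Both arms receive a home visit and a month of WhatsApp messages, so neutral satisfaction items can be put to everyone. The wording and order of the items, and whether one caller asks them all, are not given, and an article commonly leaves such detail to the full protocol. If membership is asked first, later unmasking cannot affect the answer already recorded in that call. What stands is only that the article describes no safeguard: an unblinded participant may volunteer DHC content.

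The authors can also say that self-report heads their own list of limitations, that records are out of reach, that they give a partial check, and that effectiveness is exploratory and to be interpreted with caution. All true, and it lowers the weight of the point. But the limitation as written concerns lack of verification. It does not discuss over-reporting that differs by arm.

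The baseline questionnaire has a 17-item DHC membership and utilization scale, with similar items at follow-up. Its content is not shown, so some corroborating questions may already exist. Even so, the primary outcome is fixed as the single item, and the only use of other items described is the activity check.

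Finally, baseline collection by unblinded students has little bearing on the primary outcome, because non-membership is an eligibility criterion. It affects only the accuracy of the blinding statement.

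**Conclusion.** The point holds in this form: an uncorroborated self-report from unblinded participants, with encouragement to enrol in one arm only, is open to over-reporting that differs by arm. Assessor blinding cannot prevent this, and the activity check cannot confirm members who joined without attending.

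The spurious difference is about 4 to 14 points (3.6 to 13.5) with no true effect. That rests on assumed true uptake of 10% to 28.9%, assumed over-reporting of 5% to 15% among intervention non-members, and none in control. It shows what could happen and is not an estimate. It comes from the participants' answers and should not be read as the cost of the shared call or as evidence that callers are unmasked.

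This is a cheap and worthwhile improvement to an exploratory pilot outcome, not a contradiction that undermines the design.

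**What to change.** **Main change.** Keep the self-reported item as the primary outcome. After any yes, in both arms and with the same wording, ask which DHC, the month of joining, and whether the person can read out or show a registration confirmation. Pre-specify corroborated membership as a sensitivity outcome, reported beside the self-report. Separate two grades: confirmation seen or read out, and DHC name plus month only. The second is weaker because the Visit Guide pamphlet (Table 4) already tells intervention participants about their district's DHC.

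**Secondary precautions.**
- State that the membership item is asked and recorded before any satisfaction or engagement item.
- Limit the blinding statement for outcome assessors to the follow-up telephone callers, since unblinded student interventionists conduct the baseline assessment.
- In Limitations, name over-reporting that differs by arm as a possible direction of bias.

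**Cost.** Two or three short items, a slightly longer call and a fixed item order, with no need for official records. Some true members will be left uncorroborated, so the sensitivity outcome will understate uptake. The article should say so, and should report the share of yes answers corroborated in each arm.
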